### Outcomes {12}

#### Primary outcome

The primary outcome is the mean difference between phenytoin 20% cream versus placebo cream in the 7-day average pain intensity, as measured by the NRS, over week 2 in DOBRET-positive participants.

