### Sample size {14}

We hypothesized a mean difference of 2 points on the NRS between placebo and the 20% cream (π1), and a mean difference of 1 point between 20% and 10% cream (π2). Based on preliminary data [21], we assumed for both treatment effects a standard deviation of 3.3 (standardized effect sizes: π1 = 0.61, π2 = 0.30). Using the same dataset, we conservatively assumed a correlation between NRS scores within participants (intraclass correlation) of 0.3. Seven participants per sequence (e.g. placebo–20%–10%, or 10%–placebo–20%) would be required to achieve 80% power and a two-sided significance level of 5% (= 7 × 6 sequences = 42 total sample size) [32]. Assuming a 10% drop-out rate, we will enrol 8 responding participants per group or 48 in total. DOBRET-negative participants are assumed to exhibit a mean difference of 1.5 point s (SD 4) on the NRS between placebo and the 20% cream, where 1 in 3 patients are assumed to be DOBRET-negative. This would result in a pooled overall treatment effect across DOBRET negative and positive participants of 1.83 (SD 4). Enrolling 24 DOBRET-negative and 48 DOBRET-positive participants would result in a power of 84% for the overall population.

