## Statistical methods

### Statistical methods for primary and secondary outcomes {20a}

Descriptive statistics will be used for baseline characteristics/demographics (age, sex, highest degree of education, country of birth, profession, duration and localization of pain, current neuropathic pain therapy, and past analgesic use), use of study creams (daily amount of use, number of daily applications, onset, duration and percentage of analgesic effect).

The primary endpoint measured on the NRS, as well as all other secondary endpoints, will be analysed according to the intention-to-treat (ITT) principle, incorporating all participants randomized irrespective of receiving treatment and having at least one efficacy measurement. For the primary analysis, the treatment effect will be determined in participants with a DOBRET-positive response at screening, evaluating the mean difference in NRS at week 2 between placebo and phenytoin 20% cream. Linear mixed-effects models (LME) will be used to account for the intra-individual clustering of observations. In brief, we will use an LME with fixed effects for time (week 1 or 2), treatment period (1 or 2 or 3), treatment (20% or 10% or placebo), the interaction between time and treatment, and NRS score at screening. The random part will be modelled with a random intercept and slope for time per individual, and an unstructured covariance matrix. The random slope for time will be kept in the model only if statistically significant. The likelihood ratio test will be used to test the significance of treatment; 95% confidence intervals will be based on the profile likelihood. Sensitivity analyses will be performed to evaluate (1) treatment-period interaction to assess potential carry-over effects and (2) per-protocol analysis involving all participants who completed the study. As secondary analysis, we will evaluate the treatment effect in all randomized patients irrespective of DOBRET, and explore the interaction between DOBRET outcome and treatment using additional interaction terms. Treatment effects on the NPSI, EQ-5D-5L, sBPI and PGIC will be evaluated in the same manner as the primary outcome.

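### The only test named, a likelihood ratio test of the three-level treatment factor, is not tied to the primary contrast (20% minus placebo at week 2) and, read as written, tests a different hypothesis

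*Protocol article*

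**What the plan says.** The primary outcome is a single contrast. Under Primary outcome: "The primary outcome is the mean difference between phenytoin 20% cream versus placebo cream in the 7-day average pain intensity", over week 2, in DOBRET-positive participants. The section on statistical methods {20a} repeats it as the primary analysis, "evaluating the mean difference in NRS at week 2 between placebo and phenytoin 20% cream".

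The model in the same paragraph is wider than that contrast. Besides week and period, it has fixed effects for "treatment (20% or 10% or placebo), the interaction between time and treatment, and NRS score at screening". Two statements on inference follow: "The likelihood ratio test will be used to test the significance of treatment", and "95% confidence intervals will be based on the profile likelihood". The first gives no df, contrast or week. The second names no parameter. The NPSI, EQ-5D-5L, sBPI and PGIC are to be analysed in the same way as the primary outcome.

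**The concern.** A three-level factor has 2 df, and its interaction with a two-level week adds 2 more. A likelihood ratio test of treatment therefore has three ordinary readings:

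- **2 df:** are the three creams the same?
- **4 df (main effect and interaction dropped together):** are the three creams the same in both weeks?
- **Main effect only, week 1 as reference:** are the three creams the same in week 1?

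None asks whether 20% differs from placebo at week 2. A global p-value below 0.05 could come from the 10% cream, or under the 4-df and week-1 readings from week 1, while the interval for the primary difference includes zero. The protocol does not say which result would then govern. The trial's confirmatory claim depends on the answer.

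**Working it through.** **Inputs from Sample size {14}.** "We hypothesized a mean difference of 2 points on the NRS between placebo and the 20% cream" and "a mean difference of 1 point between 20% and 10% cream", so relative effects for placebo, 10% and 20% are 0, 1 and 2. SD 3.3, intraclass correlation (ICC) 0.3, two-sided 5%, 80% power, 42 participants raised to 48. Overall population: 72 participants, effect 1.83, SD 4, stated power 84%.

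**Formulas.** Within-participant error variance is SD²(1 − ICC) = 10.89 × 0.7 = 7.623.

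- 2-df test: noncentrality λ = n·Σ(μᵢ − μ̄)² / [SD²(1 − ICC)], referred to F(2, 2n − 4) or chi-square(2).
- 1-df contrast: standard error = SD·√[2(1 − ICC)/n], referred to t or normal.

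**Step 1: the plan's own figures.** For means 0, 1, 2 the sum of squares is 2.

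| Calculation | λ or standard error | Power |
|---|---|---|
| 2 df, n = 36 | λ = 36 × 2/7.623 = 9.45 | 77% (F), 79% (chi-square) |
| 2 df, n = 42 | λ = 42 × 2/7.623 = 11.02 | 84% (F), 85% (chi-square) |
| 1 df, n = 42 | SE = 3.3√(1.4/42) = 0.602 | 91% |
| 2 df, n = 72, SD 4 | λ = 72 × 1.679/11.2 = 10.80 | 83.7% (F), 84.6% (chi-square) |
| 1 df, n = 72, SD 4 | SE = 4√(1.4/72) = 0.558 | 90% (t), 91% (normal) |

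The last two rows assume that the ICC of 0.3 carries over to the overall population. The 2-df row also needs a mean for the 10% cream, which the protocol does not give there. Taking 0.83 or 1.0 gives the sum of squares 1.679, and the midpoint 0.915 moves the power by 0.1 to 0.2 points.

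The 2-df test first passes 80% at 7 per sequence (minimum 37 by chi-square or 39 by F, rounded up to 42) and reproduces the 84%. The 1-df contrast needs only 30 (normal) or 31 (t) and does not reproduce the 84%. The 42 alone is weak evidence: a Bonferroni 1-df test and a carry-over-adjusted 1-df test (minimum 38 each) also round up to 7 per sequence. The 84% discriminates better.

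**Step 2: rejection when the primary effect is zero.** Let 20% equal placebo and 10% differ by 1 point in both weeks, with n = 48. The sum of squares is 0.667.

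- 2 df: λ = 48 × 0.667/7.623 = 4.20; rejection 42% (F) to 43% (chi-square).
- 4 df: the protocol gives no correlation r between the two weekly means of one period. The two-week mean has within-participant variance SD²[(1 + r)/2 − ICC], and chi-square(4) is used:

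| Assumed r | λ | Rejection |
|---|---|---|
| 0.3 | 8.40 | 63% |
| 0.6 | 5.88 | 46% |
| 0.9 | 4.52 | 36% |

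- 1-df contrast, 20% minus placebo: 5%, whatever the 10% cream does.

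**Step 3: power under the design effects, n = 42.** 2 df: 84 to 85%. 1 df: 91%. 4 df, equal effects in both weeks: λ = 22.04 at r = 0.3 gives 98%; λ = 11.87 at r = 0.9 gives 80%.

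**The case against.** The best defence is that the primary comparison is stated twice, the second time in the same paragraph as the test. A likelihood ratio test can have 1 df: with placebo and week 2 as reference levels, the 20% coefficient is exactly the primary contrast. A profile-likelihood interval for it would agree with that test. The article condenses a fuller plan, and coding and contrasts commonly belong in a statistical analysis plan.

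Part of this stands. The outcome definition is sound, a compliant coding exists, and the interval could carry the right inference if reported for the named difference. A reader might infer that the protocol commits the trial to an omnibus test; the text gives no df, so that is a reading and not a stated fact. But the article does not leave the test open. It names a test of a factor that it has just defined with three levels, and its own power figure fits that reading.

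Three stronger inferences also fail.

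- **A single false-positive figure of 63%.** This holds only at a week-to-week correlation of 0.3, which the protocol does not give.
- **A positive trial from week 1 alone.** At n = 48, effects of 1 and 2 points that vanish by week 2 would make the 4-df test reject in 82% of trials or more. Nothing in the protocol suggests such a course.
- **Any global test loses power.** The 2-df test does, yet still exceeds the planned 80%. The 4-df test can have more power than the contrast, because it uses both weeks.

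**Conclusion.** The point holds as a mismatch between the named test and the primary outcome; the outcome itself is correctly defined. On its ordinary reading the test answers a global or week-1 question. The size at 48 participants, with 20% equal to placebo and 10% different by 1 point, is a rejection rate of 42 to 43% (2 df) or 36 to 63% (4 df), against 5% for the right contrast. These figures rest on the protocol's SD of 3.3 and ICC of 0.3 and, for 4 df, on an assumed week-to-week correlation between 0.9 and 0.3. Power is a secondary matter: about 6 to 7 points lost with 2 df at n = 42, and no fixed direction with 4 df (about 80 to 98% against 91%). The wrong hypothesis is the main fault, and it extends to the secondary scales analysed in the same way.

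**What to change.** In the statistical methods {20a}, before unblinding, replace the sentence on the likelihood ratio test with a statement to this effect: the primary p-value is the two-sided 5%, 1-df test (likelihood ratio or Wald) of phenytoin 20% minus placebo at week 2 in DOBRET-positive participants, reported with the profile-likelihood 95% confidence interval for that same contrast; any global test of treatment is supportive. Name the contrast for the secondary scales in the same way.

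Restricted maximum likelihood (REML) with Kenward-Roger or Satterthwaite degrees of freedom is an option, not a requirement; a 1-df likelihood ratio test within the planned framework cures the fault. The cost is a sentence or two, with no extra patients or data. At the design inputs the 1-df contrast has 91% power at 42 participants and 94% at 48, so the enrolment target needs no change.

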### Trial design {8}

This is a 6-week single-centre, enriched enrollment randomized double-blind, placebo-controlled triple cross-over trial to evaluate the efficacy and safety of phenytoin cream (20% and 10%) versus placebo in 48 participants with painful CIAP. The enriched enrollment is based on a positive double-blind placebo-controlled response test (DOBRET) in 48 participants who experience within 30 minutes at least 2 points pain reduction on the 11-point numerical rating scale (NRS) on the phenytoin 10% cream applied area and at least 1 point difference in pain reduction on the NRS between phenytoin 10% and placebo cream applied area, in favour of the former. To explore to which extent and which responder definition for the DOBRET has a predictive value for sustained pain relief, an additional 24 DOBRET negative participants will be included.

Participants will be randomly allocated to one of the 6 possible intervention sequences. Participants and investigators will be blinded. The duration of each treatment period is 2 weeks. Participants will cross-over two times to each of the other treatments. The study does not have wash-out periods between treatments, because the mean duration of the analgesic effect after an application is expected to be less than 9 h [19]. A flow chart of the study is presented in Fig. 1.

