### Implementation {16c}

The GMP pharmacist is not involved in any other aspect of the study and will randomize the study medication in blocks of 6 with a randomization list generated with the Excel software programme. This will result in a balanced distribution of the labels A, B and C to the tubes with phenytoin 10%, 20% and placebo cream. The research physician will enrol the patients after performing DOBRET. The UMCU pharmacist will evaluate the outcome of the DOBRET, will stratify to DOBRET positive and DOBRET negative participants, and will randomly assign the participant to a study medication sequence (total of 6 possibilities, i.e. ABC, ACB, BAC, BCA, CAB, CBA) using a predefined randomization list.

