## Discussion

Painful CIAP results from damage of the peripheral nerves, which become hyperexcitable as a consequence of upregulation and sensitization of receptors and ion channels [34]. For example, nerve damage results in the upregulation of voltage-gated sodium channels at the nerve endings and keratinocytes [35]. Also, the presence of proinflammatory molecules due to neuronal damage is part of the hyperexcitability of neurons. Peripheral sensitization due to damage of peripheral nerves can furthermore induce central sensitization [36].

Phenytoin can influence the upregulated and sensitized receptors and ion channels in peripheral neuropathic pain. For example, phenytoin inhibits voltage-activated sodium channels, leading to reduced firing of depolarized neurons [37]. Interestingly, phenytoin blocks sodium channels poorly at slow firing rates, allowing for normal activity, but suppresses the high-frequency repetitive firing leading to pain [37]. Voltage-dependent L-type calcium channels are also inhibited by phenytoin [38]. Furthermore, phenytoin potentiates GABA-induced current through modulation of the GABAA receptor in the nanomolar range [39]. Phenytoin (IC50 = 40 μM) has 6 times stronger sodium channel binding activity, compared to lidocaine (IC50 = 240 μM) [40]. Furthermore, inhibition of peripheral sensitization can diminish and/or abolish the signs and symptoms of central sensitization due to peripheral neuropathy [41]. Thus, topical phenytoin could also influence central sensitization. The hyperexcitable nociceptors reach in the epidermis up to the stratum corneum. Molecules smaller than 500 Dalton, such as phenytoin (252 Dalton) can easily penetrate this first barrier [42]. Therefore, topical phenytoin can have an analgesic effect within some minutes, and thus, a test application can be performed to reveal responders.

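### The planned treatment-by-period interaction is close to blind to first-order carry-over in this six-sequence design; a preceding-cream term in the sensitivity analysis would estimate it directly

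*Protocol article*

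**What the plan says.** Under Trial design {8}, the protocol article states: "The duration of each treatment period is 2 weeks". The same section says: "The study does not have wash-out periods between treatments". The reason it gives is that one application should relieve pain for under 9 hours on average. Under Implementation {16c}, participants go to every order of the three creams ("total of 6 possibilities, i.e. ABC, ACB, BAC, BCA, CAB, CBA").

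Under Statistical methods {20a}, the primary model has "fixed effects for time (week 1 or 2), treatment period (1 or 2 or 3), treatment (20% or 10% or placebo"), plus time by treatment and the screening NRS. It has no term for the cream used in the preceding period. The carry-over check is a sensitivity analysis described as "treatment-period interaction to assess potential carry-over effects". The primary outcome is the 7-day average over week 2 of each period.

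**The concern.** In the two-period, two-treatment crossover, carry-over and treatment-by-period interaction cannot be told apart, so the interaction is the usual stand-in. That equivalence does not extend to three creams in six orders. Balancing the preceding cream protects the design against carry-over, and it also removes most of the carry-over signal from the treatment-by-period cell means.

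This check is the only analysis named in the article that bears on the decision to omit wash-out. If it rarely reacts to carry-over, a non-significant result says almost nothing about that decision. The same data could give a direct estimate of first-order carry-over and a 20% versus placebo difference adjusted for it.

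**Working it through.** **Inputs.** From Sample size {14}: "a mean difference of 2 points on the NRS between placebo and the 20% cream", 1 point between 20% and 10%, SD 3.3, intraclass correlation (ICC) 0.3, 7 participants per sequence, 42 in total. From {16c}: six sequences. Assumed, because the document gives no value: first-order additive carry-over into the outcome week, graded 0 after placebo, d/2 after 10% and d after 20%. Also assumed: compound symmetry, one value per period, complete data, large-sample tests.

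**The plan's own figure.** For a 2-df within-participant test of treatment with means 0, 1, 2, the non-centrality is N × Σ(mean − grand mean)² / [SD² × (1 − ICC)]. At N = 42 this is 42 × 2 / (10.89 × 0.7) = 84 / 7.623 = 11.02, with power 85%. The smallest N for 80% is 37 (chi-square) or 39 (F). Either rounds up to 42 for six equal sequences. 42 / 0.9 = 46.7, rounded up to 48. The planning figures are reproduced, so the same SD and ICC are used below.

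**Where carry-over goes in the cell means.** In periods 2 and 3, a cream's mean shifts by (sum of the three carry-overs − its own) / 2. For d = 1 the sum is 0 + 0.5 + 1 = 1.5. The shifts, as pain relief, are:

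| Cream | Period 1 | Period 2 | Period 3 |
|---|---|---|---|
| Placebo | 0 | 0.75 | 0.75 |
| 10% | 0 | 0.50 | 0.50 |
| 20% | 0 | 0.25 | 0.25 |

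Periods 2 and 3 are identical. The 20% minus placebo shift is 0 in period 1 and −0.5 afterwards, half of d. That is all the interaction can see, and it is tested on 4 df.

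**Bias of the unadjusted contrast.** Averaged over the three periods: (2/3) × (0.25 − 0.75) = −0.33, which is −d/3. For d = 2 it is −0.67, against a hypothesised effect of 2.

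**Estimability.** A model with treatment, period and preceding cream has full rank (7 parameters). By generalised least squares at N = 42, the 20% minus placebo carry-over has standard error 0.858. For graded carry-over the non-centrality of the 2-df test is (d / 0.858)². That of the 4-df interaction is 11.8% of this.

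| d (points) | Non-centrality, interaction | Non-centrality, preceding cream | Power, interaction (4 df) | Power, preceding cream (2 df) | Bias |
|---|---|---|---|---|---|
| 0.5 | 0.04 | 0.34 | 5% | 8% | −0.17 |
| 1 | 0.16 | 1.36 | 6% | 17% | −0.33 |
| 2 | 0.64 | 5.43 | 8% | 54% | −0.67 |

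With all 48 enrolled, the powers are 6% and 18% at 1 point, and 9% and 60% at 2 points.

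**Precision.** The unadjusted standard error is √(2 × 7.623 / 42) = 0.602. With the preceding-cream term it is √(0.602² + (0.858 / 3)²) = 0.667, a rise of about 11%.

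**Sensitivity to ICC.** For d = 2 and N = 42, interaction versus direct power is 11% and 67% at ICC 0.5, 19% and 88% at 0.7, and 60% and nearly 100% at 0.9. The bias of d/3 does not change.

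**The case against.** The design already limits carry-over. The effect of one application is expected to last under 9 h, and only week 2 counts, so the first week of each new cream separates the previous one from the primary outcome. Against a hypothesised 2-point effect, d = 1 means that half of it persists into days 8 to 14 after stopping, and d = 2 means that all of it does. Nothing in the article supports either size. At 0.5 points neither test is useful. This stands and limits the practical weight.

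The bias is in the safe direction: it understates 20% versus placebo, and a cream without effect leaves no drug effect to carry over. The unadjusted estimate also has the smaller mean squared error unless d exceeds about 0.86 (where d/3 equals √(0.667² − 0.602²)). This stands too, and is why the primary model should stay as it is.

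The article is condensed, and fitting details may sit in an analysis plan that is not at hand. That does not answer the point, because the article itself names both the term and its purpose.

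Three stronger readings are tempting:

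- A reader might infer from the Discussion ("Thus, topical phenytoin could also influence central sensitization") that the authors describe an effect outlasting 9 h. The sentence gives no duration.
- A reader might infer that a non-significant interaction will be cited as proof of no carry-over, or will decide which estimate is reported. The article states no such rule.
- A reader might conclude that the interaction must be dropped. It can still show treatment effects that vary across periods for other reasons, which a preceding-cream term does not.

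**Conclusion.** The point holds as a defect in a named sensitivity analysis. Under the plan's own SD and ICC, the interaction rejects barely more often than its 5% level, even when assumed carry-over equals the whole hypothesised effect (8%, against 54% for the direct term). It is not wholly blind: at an ICC near 0.9, far above the assumed 0.3, it regains useful power against large carry-over.

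The document does not show that carry-over is present or that the primary estimate is biased. The sizes used here are assumptions, and large ones are unlikely. The primary outcome, primary model and sample size are unaffected. The result rests on first-order additive carry-over, compound symmetry and complete data.

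**What to change.** In sensitivity analysis (1) of {20a}, add to the primary model a fixed effect for the cream used in the preceding period, with none in period 1. Report the carry-over estimates and the carry-over-adjusted 20% minus placebo difference, each with a 95% CI, beside the unchanged primary estimate. State that no significance test of carry-over chooses between the two; the direct term has only 17% power at 1 point, so the interval matters more than the p-value. The treatment-by-period interaction may stay as a check of effects that differ across periods, but should no longer be labelled the carry-over check.

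The cost is one model term and a wider interval in that analysis only (standard error 0.60 to 0.67 at 42 participants, 0.56 to 0.62 at 48). Conduct, schedule and sample size do not change.

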### Interim analyses {21b}

No interim analyses will be performed.

### Methods for additional analyses (e.g. subgroup analyses) {20b}

As an exploratory objective, we will determine the test accuracy for DOBRET to identify participants who benefited from treatment, where treatment benefit is defined as a 30% reduction from baseline NRS. The following factors will be tested in the models for confounding effects: pain duration, and intensity, use of co-medication and escape medication, pain characteristics, pain catastrophizing score, level of education and duration of effect of study medication. Linear regression analyses will be used to evaluate the correlation of pain reduction with pain duration, and intensity, use of co-medication and escape medication, pain characteristics, catastrophizing, level of education and duration of effect. For all analyses, results will be considered significant when *p* < 0.05. For the subgroup analysis, we will correct the *p*-value according to Bonferroni.

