## Interventions

### Explanation for the choice of comparators {6b}

In this cross-over, double-blind trial the comparator will be placebo cream applied 2 to 4 times daily according to the duration of effect. The active and placebo cream have the same white appearance and neutral smell. All participants will receive this treatment during a 2-week treatment period. Placebo cream is chosen to identify the magnitude of pain reduction attributable to the active interventions. Furthermore, a placebo cream is also used in the DOBRET to explore the predictive value of this test [21].

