### Intervention description {11a}

All participants will receive placebo, phenytoin 10% and phenytoin 20% cream, each during a period of 2 weeks. The participant will be instructed to apply the cream 2 to 4 times a day with a maximum of 1.5 g per application, measured in Finger Tip Units (FTU).

One FTU is defined as the amount of cream expressed from a tube with a 5 mm diameter nozzle, applied from the distal skin crease to the tip of the index finger, which amounts to approximately 0.5 g (see Fig. 2). The number of daily applications depends on the duration of the analgesic effect and the amount of cream depends on the size of the painful areas, e.g. both feet 1 FTU, and both feet and lower legs 3 FTU. The participant can apply the cream with bare hands, and then wash the hands after each application. After the double-blind period participants are invited to use phenytoin 20% cream in the 1-year open-label extension phase, to study the long-term pain reduction and safety.

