#### Secondary outcomes

All secondary outcomes are evaluated for phenytoin 20% versus 10% versus placebo cream in DOBRET positive, negative and all participants.

The change between baseline and week 2 for each intervention is assessed for:Pain intensity measured on theNRSNeuropathic Pain Symptom Inventory (NPSI), evaluating on the NRS neuropathic pain characteristics [27]NRS for the 3 worst pain characteristics≥30% and ≥50% improvement on the NRS compared to placebo within one participant, reflecting at least moderate and at least substantial improvement [28]Patient-reported percentage of pain reduction at the end of the second week of each interventionOnset of the analgesic effect after applicationDuration of the analgesic effect after one applicationDaily number of cream applicationsUse of escape pain medicationQuality of life measured on thesubscales of the Brief Pain Inventory (sBPI), evaluating on the NRS pain interference regarding general activity, mood, walking ability, normal work, relations with other people, sleep, and enjoyment of life [29]EQ5-5D-5L, measuring the health status on the visual analogue scale, and on a 5-point scale pain/discomfort, anxiety/depression, mobility, self-care and usual activities [30]Patient Global Impression of Change Scale (PGIC), measured on a 7-point scale [31]To evaluate the safety and tolerability of phenytoin 10% and 20% creamTolerability is defined as time-to-discontinuation of an assigned treatment since randomization.Safety is based on the safety assessments including physical examinations, clinical laboratory evaluations, vital signs and frequency of AEs or SAEs. (S)AEs will be categorized according to the Common Terminology Criteria for Adverse Events and will be rated for severity and association with the study drug.Detection of phenytoin in plasmaPredictive value of DOBRET in sustained pain reduction due to phenytoin creamTo evaluate the correlation between the PCS and the pain-reducing effect of topical phenytoin

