Furthermore, the number of participants with a minimal pain relief (MPR), defined as the minimal percentage of pain reduction in the 7-day average pain intensity, as measured by the NRS, over week 2, will be calculated, for phenytoin 10%, phenytoin 20% and placebo cream. The number of participants experiencing the following MPRs will be determined:MPR30, at least 30% improvement as moderate pain improvementMPR50, at least 50% improvement as substantial pain improvement

Regression analyses will be performed to explore associations between DOBRET results and pain reduction during the intervention periods.

The statistical analysis will be performed with SPSS 22 (SPSS Inc., Chicago, IL, USA) and with the R-project, www.R-project.org (R Development Core Team (2008). R: A language and environment for statistical computing. R Foundation for Statistical Computing, Vienna, Austria. ISBN 3-900051-07-0).

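### The exploratory DOBRET accuracy analysis counts any 30% fall from baseline as benefit, so it includes placebo response and is not reconciled with the placebo-referenced responder in the outcome list

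*Protocol article*

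**What the plan says.** Section {20b} of the protocol article defines the benefit that DOBRET is meant to identify by a single responder rule, "where treatment benefit is defined as a 30% reduction from baseline NRS". Placebo does not enter that definition. The section labels this accuracy analysis exploratory.

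Three other places bear on it:

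- The secondary outcomes list has the 30% and 50% thresholds as "improvement on the NRS compared to placebo within one participant". As a separate item, it lists the predictive value of DOBRET for sustained relief caused by phenytoin cream. The list opens with "The change between baseline and week 2 for each intervention is assessed for".
- Section {20a} counts participants reaching 30% (MPR30) and 50% (MPR50) improvement. These counts "will be calculated, for phenytoin 10%, phenytoin 20% and placebo cream", and no reference value is named.
- Section {20a} also plans, in the mixed model, to "explore the interaction between DOBRET outcome and treatment using additional interaction terms".

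On the role of placebo, section {6b} says "Placebo cream is chosen to identify the magnitude of pain reduction attributable to the active interventions". On data availability, section {11a} says "All participants will receive placebo, phenytoin 10% and phenytoin 20% cream, each during a period of 2 weeks".

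**The concern.** A test-accuracy analysis is only as good as its reference standard. The question is which participants obtain relief from phenytoin. A fall from baseline also contains placebo response, expectation, natural fluctuation and regression to the mean, the last because entry requires a weekly mean NRS of at least 4. Under the {20b} rule all of this is credited to the cream.

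The index test is itself placebo-controlled: a positive DOBRET needs at least 1 point more relief on the phenytoin area than on the placebo area. It would then be judged against a standard that does not subtract placebo, although the crossover gives each participant a placebo period.

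At stake is how the sensitivity, specificity and predictive values of DOBRET can be read. They would describe prediction of improvement while using phenytoin, not of improvement because of it.

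**Working it through.** The protocol states no sample size, precision or expected value for DOBRET accuracy, so there is no figure of its own to reproduce.

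**1. Can the two references disagree for one person?** Illustrative scores:

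| Baseline | Placebo, week 2 | Phenytoin, week 2 | Fall from baseline | Improvement vs own placebo |
|---|---|---|---|---|
| 6 | 4 | 4 | (6 − 4)/6 = 33%: benefit | (4 − 4)/4 = 0%: no benefit |
| 6 | 7 | 4.5 | (6 − 4.5)/6 = 25%: no benefit | (7 − 4.5)/7 = 36%: benefit |

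They can, and in both directions.

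**2. How often would placebo alone meet the {20b} rule?**

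From the protocol: a 2-point effect of 20% cream over placebo, and an SD of 3.3 (sample size section {14}). Assumed: baseline NRS 6, normally distributed falls, SD of change 2 to 3.3, and a mean placebo fall m of 0, 1 or 2 points.

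The threshold is 0.3 × 6 = 1.8 points, so P(benefit) = 1 − Φ((1.8 − m)/SD).

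| Period | m | SD 2 | SD 3.3 |
|---|---|---|---|
| Placebo | 0 | 1 − Φ(0.90) = 18% | 1 − Φ(0.55) = 29% |
| Placebo | 1 | 1 − Φ(0.40) = 34% | 1 − Φ(0.24) = 40% |
| Placebo | 2 | 1 − Φ(−0.10) = 54% | 1 − Φ(−0.06) = 52% |
| 20% cream | 1 + 2 = 3 | 1 − Φ(−0.60) = 73% | 1 − Φ(−0.36) = 64% |

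With a 1-point placebo fall, the placebo rate is 34.5/72.6 = 47% of the 20%-cream rate at SD 2, and 40.4/64.2 = 63% at SD 3.3.

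**3. How do the two rules compare within participants?**

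A simulation drew baseline, placebo and 20%-cream scores. Assumed: mean baseline 6.5, scores limited to 0–10, score SD 1.5, 2 or 3.3, and within-participant correlation 0.3 or 0.6. Entry was restricted to the protocol's range of 4 to below 10.

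Share labelled as benefiting when phenytoin has no effect:

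| Mean placebo fall | 30% below baseline | 30% below own placebo |
|---|---|---|
| 0 | 5–29% | 5–26% |
| 1 to 2 points | 22–53% | 8–34% |

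With the protocol's planning values (effect 2, SD 3.3, correlation 0.3) and a placebo fall of 0, 1 or 2 points:

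- About 35%, 46% or 57% of those labelled as benefiting on 20% cream would also meet the 30% criterion on placebo.
- 24–28% of those labelled as benefiting are not 30% better than their own placebo score.

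The baseline rule therefore performs worse as placebo response grows. If there is no mean fall on placebo, the two rules have similar error rates. The placebo-referenced rule is not free of error in any scenario.

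**The case against.** The strongest case on the other side has five parts.

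- **No plain contradiction.** A reader might infer that {20b} contradicts the outcome list. The list does not name the placebo-referenced responder as the reference standard for DOBRET; the two are separate items. Its opening words also refer to change from baseline. This stands: the text shows an unreconciled 30% definition, not a contradiction.
- **The main secondary objective does not rest on this analysis.** A reader might infer that the whole assessment of DOBRET is compromised. Accuracy is labelled exploratory, and the DOBRET-by-treatment interaction in {20a} is placebo-controlled and uses the continuous NRS. This stands too. The interaction, however, tests whether the mean effect differs between groups and does not supply sensitivity or specificity, so it does not replace a sound accuracy analysis.
- **No direction of bias is shown.** It is tempting to say that DOBRET will look better because it selects general improvers, or worse because placebo responders fall in both groups. The calculations give responder rates only. DOBRET's own placebo contrast works against selecting general improvers. Neither direction can be claimed.
- **The per-cream responder counts are sound.** Counting MPR30 and MPR50 on each cream, with placebo as control, is an ordinary controlled comparison. Referring those counts to the placebo period would make the placebo count meaningless. They should not be rewritten.
- **The alternative is noisy.** A ratio of two single-period scores misclassifies as well, as the 5–34% range with no drug effect shows. It lessens the problem when there is a placebo response, but does not remove it.

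That {20b} does not say which strength defines benefit is detail an article may leave to the full protocol or analysis plan, and is not raised as a fault.

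**Conclusion.** The point holds in limited form. As written, the exploratory accuracy analysis treats any 30% fall from baseline as benefit from treatment, so placebo response and regression to the mean enter the reference standard. This fits poorly with the listed aim of predicting relief caused by phenytoin, and with the placebo-referenced 30% responder given elsewhere.

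Under the assumptions shown, 18–54% of participants would meet the rule on placebo, for a mean placebo fall of 0 to 2 points. The baseline level, the placebo fall and the lower SDs are assumptions, so this is a range and not an estimate. The effect on sensitivity and specificity has not been quantified. The primary outcome, the mixed-model treatment comparisons and the DOBRET-by-treatment interaction are unaffected. This is an inexpensive improvement to one exploratory analysis.

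**What to change.** In {20b}, define benefit for DOBRET accuracy as a week-2 7-day mean NRS on phenytoin at least 30% lower than in the participant's own placebo period, in line with the responder in the secondary outcomes list.

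Keep the fall-from-baseline version as a supportive analysis, and also run it on the placebo period as a negative control. If DOBRET predicts a 30% fall on placebo about as well as on phenytoin, the baseline version is not measuring response to the drug.

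In {20a}, leave the MPR30 and MPR50 counts for all three creams unchanged, and state that their reference is baseline.

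The cost is wording; no new data are needed. There are two drawbacks. Participants missing either the phenytoin or the placebo period drop out of the binary measure. The ratio of two single-period scores is itself noisy, and the report should say so.
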